#### Analysis

Using the Consolidated Standards of Reporting Trials (CONSORT) flow chart (Figure 1) (20), we will describe the number of screened patients, those meeting inclusion and exclusion criteria, the number consented, and numbers of those who withdrew consent. In addition, we will provide in the text details of the consent process, including proportion of children with prospective consent vs. consent to continue, reasons why consent to continue was used, and time from enrolment to obtaining written consent in hours (IQR). Time from randomisation to initiation of allocated treatment will be reported. Descriptive statistics will be utilised to report on demographics, clinical history and baseline clinical characteristics of patient allocated to each of the study arms (Supplementary Table 1). Statistical comparison between the characteristics of the two arms at baseline will not be undertaken. The feasibility and clinical outcome measures (Supplementary Tables 2, 3) will be compared with the estimate of the difference and corresponding 95% confidence intervals (CIs). Continuous outcomes are assumed to be non-normally distributed, and as such quantile regression will be used to generate the CIs. A test of two proportions will be used for the binary outcomes. Analyses will be by intention-to-treat. Adverse events will be presented descriptively (Supplementary Table 4).

We will graphically compare physiological measures, heart rate, systolic blood pressure, pulse pressure (systolic minus diastolic blood pressure), shock index (heart rate divided by systolic blood pressure) and use of fluid bolus volume (in ml/kg) over time, using values measured during the first 24 h, comparing the intervention group to the control group, using values measured during the first 24 h.

We anticipate that <30% of RESPOND ED study patients will be co-enrolled into a concomitant study investigating metabolic resuscitation, named RESPOND PICU (ACTRN12619000829112) (27). Given that the study is a pilot feasibility study, analyses on RESPOND ED will occur separately from RESPOND PICU.

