## Methods

### Study Design and Setting

The RESPOND ED study is a pilot multicentre, open label, pragmatic randomized controlled trial (RCT) for children aged between 28 days and 18 years treated for septic shock (Figure 1). The study will recruit across four tertiary Emergency Departments (ED) and Paediatric Intensive Care Units (PICU) of participating sites in Queensland, Australia. The trial compares***early inotropes*** defined as adrenaline infusion started after 20 mL/kg fluid resuscitation, with ***standard care*** defined as providing up to 40–60 mL/kg fluid resuscitation prior to initiation of inotropes (11, 13). The study protocol has been approved by the Children's Health Queensland Hospital and Health Service Human Research Ethics Committee (HREC/18/QCHQ/49168) and registered with the Australian New Zealand Clinical Trials Registry (ACTRN12619000828123, June 2019). The trial abides by the Standard Protocol Items: Recommendations for Interventional Trials (SPIRIT) guidelines (20).

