### Randomisation

Patients will be allocated in a 1:1 ratio to the treatment group and standard care group (receiving early inotropes vs. standard fluid management). A permuted block randomisation method with variable block sizes of two, four and six and stratified by site will be used to allocate eligible patients to a study group. Randomisation will be performed by the site investigator, research coordinator or treating clinician by opening the next sequential sealed opaque envelope which are prepared using a randomisation sequence prepared by The University of Queensland, Brisbane, Australia.

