### Statistical Analysis Plan

#### Sample Size

A recruitment period of 24 months is the projected time to achieve the required sample size of 40 participants. The size of the pilot (*N* = 40) was chosen to reflect about 10% of a full trial to yield sufficient data in relation to feasibility. We estimate that ~50 children each year are treated for septic shock in the main participating ED. Assuming that 30–40% of children will meet exclusion criteria, and anticipating 50% enrolment rates, completion within 24 months is projected to be feasible.

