## Discussion

Resuscitation with intravenous fluid boluses represents a key element of paediatric sepsis treatment bundles (11, 13, 28). Despite the pathophysiological rationale for liberal fluid resuscitation, there is limited evidence for this practice, and potential for harm. Subsequent to the FEAST study conducted in a low resource environment where intensive care support was not available, no similar study powered for clinical endpoints was performed in high income settings (14, 29). As a result, current pediatric Surviving Sepsis Campaign guidelines maintained the recommendation to administer a 40–60 ml/kg fluid bolus in settings where intensive care is available, based on expert opinion rather than robust evidence (11).

Different to other pilot studies on the use of fluid in critically ill children with sepsis, which primarily regulated the amount of fluid to be administered (30, 31), the study protocol stipulates the early use of adrenaline rather than prescribing how much fluid should be administered thereafter. The present pilot study was designed to capture feasibility, process of care measures, and robust severity measures. In addition, the study encompasses a comprehensive follow-up of study patients at 28-days and at 6-months to assess patient-centred outcomes such as quality of life. The pragmatic study design, embedded in an established pediatric sepsis pathway, intends to facilitate enrolment to address challenges which have been observed in other fluid trials in children with sepsis (30, 31). However, the study sample size will not permit to conduct pre-planned adjusted analyses on clinical outcomes and the study is not designed to assess the impact of co-interventions such as steroids.

In summary, this pragmatic pilot study design will provide urgently needed data to inform feasibility and design of a full trial powered to assess benefit of early inotropes in sepsis.

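### Site is used to stratify randomisation but is named in no comparison, and the interval for binary outcomes is left open to a Wald form that is unreliable with 20 children per arm

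*Protocol article*

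**What the plan says.** Under Randomisation, children are allocated 1:1 in permuted blocks with "variable block sizes of two, four and six and stratified by site". Study Design and Setting plans four emergency departments, and Sample Size gives a "required sample size of 40 participants", so about 20 per arm.

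Under Statistical Analysis Plan, Analysis, feasibility and clinical outcomes are to be reported as a between-arm difference with a 95% CI. Continuous outcomes get their intervals from quantile regression, with no covariates named. For the rest, "A test of two proportions will be used for the binary outcomes"; neither the version of the test nor the interval method is given. Adverse events are descriptive only.

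The Discussion says that "the study sample size will not permit to conduct pre-planned adjusted analyses on clinical outcomes". Table 2 lists 24 h fluid volume and time to inotropes as feasibility outcomes. The text after it sets the marks of feasibility: a separation of at least 10 mL/kg in bolus fluid over 24 h and at least 20 min in inotrope start.

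**The concern.** There are two separate issues.

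**Site.** Stratifying by site balances the arms within site. An analysis that ignores site leaves between-site variation in the residual, so the interval tends to be wider than the design requires. This matters most for the two feasibility comparisons, because they are read against numerical thresholds and the Discussion's reason for not adjusting does not reach them. Time to inotropes appears in Table 2 only as a feasibility outcome. Fluid volume appears there and again among the proxy efficacy measures.

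**Binary outcomes.** The compared binary outcomes include 28-day mortality and the proportions with lactate below 2 mmol/L. Deaths may be very few with 20 per arm. The interval that commonly accompanies a two-proportion z test (Wald) behaves badly there. A mortality difference reported as exactly zero with no uncertainty would mislead those designing the full trial.

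**Working it through.** **Inputs from the article.** N = 40, 1:1, so 20 per arm; site as stratum; four planned sites; 95% CIs. N was set as about 10% of a full trial, with no power, SD, event rate or between-site variance behind it. There is therefore no figure of the plan's own to reproduce. All rates, SDs, ICCs and site sizes below are assumptions, shown as ranges.

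**1. Binary outcomes, observed intervals.** Wald: d ± 1.96 × √[p₁(1−p₁)/20 + p₂(1−p₂)/20]. Newcombe combines the two single-arm Wilson limits; for 0/20 the Wilson upper limit is 1.96²/(20 + 1.96²) = 3.84/23.84 = 16.1%.

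| Events per arm | Wald (points) | Newcombe (points) |
|---|---|---|
| 0 vs 0 | 0 to 0 | −16.1 to +16.1 |
| 0 vs 1 | −14.6 to +4.6 | −23.6 to +11.6 |
| 0 vs 4 | −37.5 to −2.5 | −41.6 to +0.1 |

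The chance of no events in either arm at a common risk p is (1−p)⁴⁰: 0.95⁴⁰ = 12.9%, 0.97⁴⁰ = 29.6%, 0.98⁴⁰ = 44.6%.

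**2. Binary outcomes, true coverage of a nominal 95% interval.** Exact enumeration of all 21 × 21 outcomes:

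| True risks | Wald | Newcombe |
|---|---|---|
| 2% vs 5% | 75.6% | 99.8% |
| 2% vs 8% | 79.9% | 99.6% |
| 5% vs 10% | 85.8% | 98.6% |
| 5% vs 20% | 91.3% | 96.3% |
| 2% vs 2% | 99.9% | >99.9% |
| 5% vs 5% | 98.8% | 99.8% |
| 50% vs 50% | 91.9% | 95.8% |

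At 2% vs 5% the no-event result has probability 0.98²⁰ × 0.95²⁰ = 23.9%, which accounts for nearly all of the 24.4% non-coverage. When the risks are equal, the same (0, 0) interval happens to contain the true difference of zero, so Wald over-covers. The pooled z test itself holds its size (maximum 5.3% over all common rates, 1.2% at 5%). The weakness is in the interval, not the test.

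**3. Site, linear model.** Assume site sizes 22/8/6/4 and residual SD 10 mL/kg (variance 100). The expected between-site sum of squares is σ_b² × (N − Σnᵢ²/N), where N − Σnᵢ²/N = 40 − 600/40 = 25.

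- Between-site SD 5 (ICC 25/125 = 0.20): unadjusted residual variance ≈ 100 + 25 × 25/38 = 116.4. Unadjusted SE relative to a model with every site: √1.164 = 1.08. Simulation gives SEs of about 3.38 vs 3.16, about 7%.
- Between-site SD 2.5 (ICC 6.25/106.25 = 0.06): 100 + 6.25 × 25/38 = 104.1, ratio 1.02. Simulation gives 1.6%.
- ICC 0: no gain; the unadjusted SE is about 0.4% smaller.

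A central-vs-others indicator recovers only part of this, because variation among the three smaller sites stays in the residual: 18 − (64 + 36 + 16)/18 = 11.56. At ICC 0.20 the residual variance is 100 + 25 × 11.56/37 = 107.8, so the ratio is √(116.4/107.8) = 1.04. At ICC 0.06 it is √(104.1/101.95) = 1.01. The gain is about half that of the full set of site terms.

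**4. Site, median regression (the planned method).** Simulated mean CI widths in mL/kg without and with site terms, assuming SD 20 and sites 20/8/6/6:

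| ICC | Normal errors | Lognormal errors |
|---|---|---|
| 0 | 37.6 → 35.6 | 23.4 → 22.1 |
| 0.05 | 37.2 → 34.6 | 24.3 → 21.8 |
| 0.20 | 36.3 → 31.9 | 26.6 → 20.0 |

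The 5% to 6% narrowing at ICC 0 is a small-sample artefact, since there is no site effect to remove. At ICC 0.20 the total narrowing is 12% to 25% with four sites and 6% to 12% with two (30/10). Unadjusted coverage was 97% to 99.5%, so the intervals are conservative.

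**The case against.** The strongest reply is that the article does not say Wald, or even large-sample. A Fisher test or a score interval would fit its wording, and an article may leave the formula to a fuller plan. That is right as far as it goes: a reader might infer that the plan's binary intervals are wrong, and the document does not support this. What stands is narrower. The article presents its own statistical analysis plan and says how the continuous intervals are produced, yet for binary outcomes it promises an interval and names only a test.

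On site, the Discussion gives a reason for not adjusting clinical outcomes, and in a 40-child pilot it is a fair one. For the feasibility outcomes the Analysis section is silent; it does not exclude site. A reader might also infer that the fluid interval is needlessly wide. That cannot be shown, because no between-site variance is given. The Introduction's remark on variable local practice is general background. Screening and Consenting describes one statewide pathway used at every site, and Standard Care describes shared education since 2018. Both point to smaller site differences, although standard care still follows site-specific protocols.

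Last, site-stratifying a rare binary outcome over four small sites is barely workable. This is accepted, and no such analysis is asked for.

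**Conclusion.** The point holds in a limited form. The stratification factor is absent from the stated comparisons, and the reason offered for not adjusting does not cover the two outcomes on which feasibility is judged. The consequence is possible loss of precision, not bias or invalid coverage. It runs from nothing at ICC 0 to about 7% in a linear-model SE at ICC 0.20 with all site terms, and about 4% with a single central-vs-others term. Median regression may gain more if site differences are large.

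For binary outcomes the problem is conditional on Wald being used. It would then give a zero-width interval with no events and coverage of about 76% to 86% at unequal rare risks (2% vs 5% to 5% vs 10%), but over-coverage at equal rare risks. Event rates, SDs, ICCs and site sizes are all assumed. The trial makes no power claim and attaches no stated decision to the mortality interval, so this is a worthwhile clarification and not a threat to its conclusions.

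**What to change.** 1. In the Analysis section, include site in the quantile regressions for 24 h fluid volume and time to inotropes. Fix it in advance as central site vs others, so that the model does not depend on how many children each small site recruits.
2. For fluid volume, add pre-randomisation bolus volume as a covariate. Table 3 lists treatment received among the baseline data, and eligibility allows it to range from 20 to just under 40 mL/kg. Its benefit cannot be sized from the document.
3. For binary outcomes, report the unstratified risk difference with a named score-type interval (Newcombe or Miettinen–Nurminen).
4. Leave the Discussion sentence as it stands for clinical outcomes.

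The cost is a few sentences and a few lines of code, with no new data. The site term uses one degree of freedom out of 40 children. Score-type intervals will be wider and conservative for rare events (coverage 98.6% to 99.8% in the unequal rare-risk cases from 2% vs 5% to 5% vs 10%), which is a small price for avoiding a zero-width result.

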### Current Trial Status

RESPOND ED commenced recruiting in July 2019 with a projected completion date of July 2021. Recruitment is live at the central study site Queensland Children's Hospital, and at Gold Coast University Hospital. Expansion to further centres has been delayed due to the COVID-19 pandemic.

## Discussion

Resuscitation with intravenous fluid boluses represents a key element of paediatric sepsis treatment bundles (11, 13, 28). Despite the pathophysiological rationale for liberal fluid resuscitation, there is limited evidence for this practice, and potential for harm. Subsequent to the FEAST study conducted in a low resource environment where intensive care support was not available, no similar study powered for clinical endpoints was performed in high income settings (14, 29). As a result, current pediatric Surviving Sepsis Campaign guidelines maintained the recommendation to administer a 40–60 ml/kg fluid bolus in settings where intensive care is available, based on expert opinion rather than robust evidence (11).

Different to other pilot studies on the use of fluid in critically ill children with sepsis, which primarily regulated the amount of fluid to be administered (30, 31), the study protocol stipulates the early use of adrenaline rather than prescribing how much fluid should be administered thereafter. The present pilot study was designed to capture feasibility, process of care measures, and robust severity measures. In addition, the study encompasses a comprehensive follow-up of study patients at 28-days and at 6-months to assess patient-centred outcomes such as quality of life. The pragmatic study design, embedded in an established pediatric sepsis pathway, intends to facilitate enrolment to address challenges which have been observed in other fluid trials in children with sepsis (30, 31). However, the study sample size will not permit to conduct pre-planned adjusted analyses on clinical outcomes and the study is not designed to assess the impact of co-interventions such as steroids.

In summary, this pragmatic pilot study design will provide urgently needed data to inform feasibility and design of a full trial powered to assess benefit of early inotropes in sepsis.

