Physiological parameters and study treatment (fluids and inotropes) will be collected upon randomisation, then at 20-min intervals during the first 4 h, and at six, 12 and 24 h subsequently. The total fluid given will be captured at one, four, 12 and 24 h. Organ dysfunction and organ support will be collected upon randomisation, by 24 h and thereafter daily whilst treated in PICU for a maximum of 28 days. In addition, we will capture initiation of antibiotic therapy, intravenous steroids, duration of inotrope and/or vasopressors and respiratory support, PICU discharge, hospital discharge, death and cause of death. Protocol deviations and reasons for such will be recorded.

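### Forty children do not rule out adjusting the primary clinical outcome for one prespecified baseline value, and pSOFA at randomisation is already due to be collected

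*Protocol article*

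**What the plan says.** The protocol article presents itself as giving both the protocol and the statistical analysis plan (Introduction).

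- **Discussion:** among the limitations, "the study sample size will not permit to conduct pre-planned adjusted analyses on clinical outcomes".
- **Analysis:** "Continuous outcomes are assumed to be non-normally distributed, and as such quantile regression will be used to generate the CIs". Binary outcomes get a test of two proportions. Results are differences with 95% confidence intervals, by intention to treat. No covariate is named.
- **Study Outcomes and Table 2:** the primary clinical outcome counts days alive without organ dysfunction up to day 28. Deaths within that time score zero, and dysfunction means a pSOFA score above zero.
- **Data Collection:** "Organ dysfunction and organ support will be collected upon randomisation", then by 24 hours and daily in PICU. Table 3 lists severity among the baseline data and names pSOFA for the daily assessments.
- **Randomisation:** "Patients will be allocated in a 1:1 ratio to the treatment group and standard care group", stratified by site only.
- **Sample Size:** "the required sample size of 40 participants" "was chosen to reflect about 10% of a full trial to yield sufficient data in relation to feasibility".

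**The concern.** The Discussion gives sample size as the reason why no adjusted analysis of clinical outcomes can be planned. That is a reason against models with several covariates, and against adjusting an outcome with very few events. It is not a reason against one prespecified baseline covariate in the model for a day count. The planned quantile regression can take such a covariate without a change of method.

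Days free of organ dysfunction plausibly depend on how much dysfunction the child had at entry. Nothing in the design balances severity: stratification is by site alone, and under Screening and Consenting no physiological threshold for shock is required. An unadjusted difference therefore moves with any chance difference in entry severity. At stake is the precision of the pilot's main clinical estimate, which the Discussion says will help to design the full trial.

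**Working it through.** **The plan's own figure.** N = 40 comes with no effect size, standard deviation, power or full-trial size, so it cannot be re-derived. The sample-size arithmetic offered concerns accrual and has no bearing here. With 1:1 allocation, 40 children give 20 per arm.

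**Step 1. Cost of one covariate in a linear model.** Residual degrees of freedom fall from 40 − 2 = 38 to 40 − 3 = 37, and the critical t rises from 2.024 to 2.026. With baseline–outcome correlation ρ and n = 40, the expected ratio of adjusted to unadjusted interval width is about

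√[(1 − ρ²) × (1 + 1/(n − 4))] × t(0.975; 37)/t(0.975; 38).

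At ρ = 0 this is √(1 + 1/36) × 2.0262/2.0244 = 1.0138 × 1.0009 = 1.015. The worst case is thus a loss of about 1.5%.

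**Step 2. Gain in a linear model.** The documents give no ρ, so a range is assumed.

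| ρ (assumed) | Width ratio |
|---|---|
| 0 | 1.015 |
| 0.1 | 1.010 |
| 0.2 | 0.994 |
| 0.3 | 0.968 |
| 0.5 | 0.879 |
| 0.7 | 0.725 |

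The ratio crosses 1 at |ρ| of about 0.17.

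**Step 3. The planned method.** Median regression was simulated with and without baseline pSOFA, using 1,000 trials of 20 per arm for each scenario and no treatment effect. All inputs are assumptions:

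- pSOFA is negative binomial with mean about 5, capped at 20.
- Days of dysfunction are log-normal (log-mean 1.2 at pSOFA 5, log-SD 0.9), rounded to whole days.
- The death risk is 6% at pSOFA 5, and deaths score zero.
- In the last three scenarios, duration and death risk both rise with pSOFA.

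| Size of correlation | Median width ratio | Trials with wider adjusted interval | Ratio of SDs of the estimate | Adjusted coverage |
|---|---|---|---|---|
| 0 | 1.00 | 60% | 0.99 | 96.7% |
| 0.23 | 0.98 | 43% | 0.87 | 97.9% |
| 0.44 | 0.90 | 27% | 0.77 | 98.3% |
| 0.59 | 0.82 | 18% | 0.68 | 99.2% |

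Every fit converged. The typical reported interval narrows by about 2%, 10% and 18% in the last three rows.

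**Step 4. Chance imbalance.** The probability that the arms differ by more than d SD in a baseline value is 2 × [1 − Φ(d/√(2/20))].

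- d = 0.5: 0.5/0.316 = 1.58, so 0.114.
- d = 0.25: 0.25/0.316 = 0.79, so 0.429.

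**The case against.** The case for leaving the plan alone is respectable. A comparison of randomised arms without covariates is valid, so nothing is biased. The trial is a feasibility pilot and claims no power for a clinical outcome. Feasibility is judged by fluid separation and time to inotropes, which adjustment of the clinical outcome does not touch. The sentence sits among the limitations and may have been meant for multivariable modelling, which 40 children do limit. All of this stands and keeps the consequence modest. It does not make the stated reason correct for one covariate, and the clinical differences will still be reported with confidence intervals.

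A reader might infer more than the documents support:

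- **That adjustment is sure to narrow the interval.** This depends on a correlation that the documents do not give. The simulated fall in the SD of the estimate (13%, 23% and 32%) is larger than the fall in the typical interval width, but a reader of the trial sees one interval, and that can come out wider.
- **That it removes severity imbalance.** It deals only with the part that pSOFA captures under a linear term.
- **That no clinical outcome is limited by 40 children.** With few deaths, 28-day mortality is.
- **That the score must precede study adrenaline because an earlier inotrope infusion is an exclusion (Table 1).** The exclusion shows only that no inotrope infusion was begun before enrolment. Whether the score's components are measured before study adrenaline, which starts straight after randomisation, rests on the collection time given under Data Collection.

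A baseline pSOFA is itself an inference from Study Outcomes and Data Collection read together, and its completeness in the emergency department is not stated.

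**Conclusion.** The point holds in a limited form. N = 40 does not preclude adjusting the continuous primary clinical outcome for one prespecified baseline value, so the Discussion's reason is too broad. The cost is one degree of freedom and at most about 1.5% of expected linear-model width.

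The benefit is conditional. If baseline pSOFA is prognostic, with an assumed correlation of about 0.23 to 0.6, median regression gives a typical interval about 2% to 18% narrower. At zero correlation there is no gain. The sizes rest on the simulation's assumptions, since the documents supply neither the correlation nor the distribution of the outcome. Adjustment would also account for chance imbalance in pSOFA itself (probability 0.11 of a difference above 0.5 SD), and for no other severity difference.

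This is a worthwhile, cheap improvement to a valid analysis. It does not show that the planned comparison is wrong.

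**What to change.** 1. In the Discussion, restrict the sentence to sparse binary outcomes and multivariable models.
2. In the Analysis section, prespecify total pSOFA at randomisation as a single linear covariate in the quantile regression for organ-dysfunction-free days to day 28, and for other outcomes analysed as day counts.
3. State that the score uses only values recorded before study treatment starts.
4. Report the unadjusted estimate beside the adjusted one.
5. Leave 28-day mortality unadjusted, and add no further covariates.

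The cost is wording, because collection at randomisation is already scheduled. The small downside is that a rule, the same in both arms, must be fixed in advance for pSOFA items not measured at randomisation.
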